#### Intervention arm core clinic components

Overarching strategies are outlined in Table 2. Once the clinic is assigned to the intervention arm, they will be asked to designate two clinic champions per clinic including one physician or advanced practice provider (APP) and one person who would manage daily workflows such as a practice manager or senior medical assistant. These individuals will complete a survey on organizational readiness to change [28]. Champions will also answer basic questions about workflow related to CRC screening. Within the first month of rolling out the program at a new clinic the patient navigators and study team members will schedule a site visit to review project goals including cultural tailoring and relevance for Black and Hispanic/Latino populations, provide provider and patient facing materials about the navigation program, and complete any baseline clinic level assessments that may affect how the navigation program is delivered. Providers will be asked to refer Black and Hispanic/Latino patients age 45 to 75 years old who have previously missed screening or require assistance to complete screening due to transportation, stigma, health literacy, or other barriers.

**Table 2 Tab2:** Example implementation strategies

Strategy category	Individual strategy	Study application
Evaluative and iterative	Assess for readiness and identify barriers and facilitators	Clinic level assessments upon joining the intervention arm
	Audit and provide feedback	Utilize internal dashboard to provide regular updates on CRC screening by race/ethnicity to providers within intervention clinics
Develop stakeholder relationships	Build a coalition	Work with the community advisory board to understand root causes of disparities, review proposed intervention materials, ongoing review to best serve community members
Engage consumers	Intervene with patients to enhance uptake and adherence	Conduct formative interviews with patients and collect ongoing feedback on experiences with intervention; outreach by phone and patient portal
Change infrastructure	Change record systems	Utilize OMOP Common Data Model to define outcome; create referral orders specific to individual primary care sites
Train and educate stakeholders	Conduct educational meetings with stakeholders	Meet with clinical champions including physicians and administrators to review project goals and solicit feedback; engage system leadership

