During the six-month active support period, the study team will review weekly data and will reach out to clinics if two sequential weeks of continuous data during the six-month of active support period show that providers are not referring eligible patients to navigation in order to meet the minimum sample size of 20 patients per clinic per six months. We will meet with the clinical champions first and if needed will conduct additional site visits to troubleshoot, develop additional supportive materials, or consider how communication or reminders through the electronic health record (EHR) might be needed to support referrals to patient navigation. Conversely, it is possible that we will receive too many referrals, whereby it appears that providers are referring everyone due for screening rather than those who have a history of not completing screening or identified barriers to screening. If this is the case, we will consider providing decision support tools for triaging who needs referral or creating a system within our team to stratify intensity of support based on the number of previous referrals/orders that were incomplete or identification of social needs in the medical record.

The research team will review data bi-weekly and communicate with the clinical champions at least monthly during the initial six months in the intervention arm. This data will include progress of CRC patient navigation referrals and completion of screening. After the six-month intensive support, they will receive quarterly updates on CRC screening completion rates overall and by provider, broken down by patient race/ethnicity.

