### Patient navigation- Patient-level component

#### Patient eligibility and initial CRC outreach

Patients will be eligible if they are 45 to 75 years old, identify as Hispanic/Latino and/or Black, are not up to date on CRC screening recommendations, and have had at least one primary care visit at the included clinics in the past 365 days. The target population of patients who are due for screening is intended to align with the quality metrics relevant to CRC screening in the healthcare system. While we are not limiting to annual well visits, we will conduct sensitivity analyses to understand how reason for a visit affects screening referral, navigation referral, or completion outcomes. For clinics in the intervention phase, the provider will have the option to refer patients to navigation. Two days prior to their primary care appointment, patients will receive a reminder via text message indicating that their CRC screening is due and encouraging them to talk to their doctor about CRC screening.

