#### Secondary outcomes

We will also assess implementation outcomes including reach and adoption of the culturally tailored navigation intervention. Reach will be assessed as the percentage of eligible Black and Hispanic patients at each clinic who received a referral for navigation, and of those referred, who engaged with navigation. While we will look at overall reach, we will also calculate the number of people referred among those who have previously failed to complete screening referrals/orders to better understand navigation referral for those who are at higher risk of non-compliance. We will consider intersectional factors affecting reach such as patient insurance, age, race/ethnicity, and primary language. Adoption will be assessed by the percentage of providers who referred eligible patients for navigation. Each of these outcomes will also be examined separately for Black and Hispanic/Latino patients.

We will solicit feedback from clinical champions both on patient navigation and the implementation strategies (engaging patients, clinic assessments and tailoring, audit and feedback loops) via annual surveys. Surveys will include questions on acceptability, feasibility, and appropriateness using a validated 12-item scale, [42] the Clinical Sustainability Assessment Tool, [43] questions on satisfaction with the SCREEN programs, and suggestions for improvement. At the end of the trial, we also will conduct interviews with one or two representatives from each clinic site to understand how the intervention and implementation strategies addressed or failed to address contextual barriers to navigation implementation.

To track changes to the implementation strategies, or clinic-level delivery of navigation, we will adopt the Longitudinal Implementation Strategy Tracking System (LISTS, Table 4) [44], which incorporates implementation science strategy reporting and specification standards, [45] and the framework for documenting modifications to implementation strategies (FRAME-IS), [46] to understand how an intervention is being delivered and iteratively adapted across diverse settings. These methods will support the documentation of the implementation strategies so that we can better understand implementation of a patient navigation program for historically underserved populations across clinics with different baseline characteristics.

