### Data analysis plan

Baseline characteristics of the patients in the intervention and control groups will be summarized first in a traditional way (intervention vs control) using means, standard deviations for continuous variables and frequencies and percentages for categorical variables. Exploratory descriptive analyses will also be conducted using clinic level data for six-month periods to examine patient characteristics to ensure a balanced design in an intent-to-treat (ITT) framework. Initial comparisons between the intervention and control groups will be done using two-sample test statistics such as t-test and Chi-square as appropriate. The effectiveness of the intervention will be assessed based on the primary patient-level outcome, screening completion, which is measured as a binary variable indicating whether a patient identified as “due for screening” completed CRC screening, and will be analyzed using Generalized Linear Latent and Mixed Models [49] suitable for categorical, ordered or count outcomes with random effects at multiple levels since observations will be nested in clinics and clinics will be exposed to intervention at different time points. The model will include a treatment indicator, a fixed effect for time (steps) and their interactions to account for the potentially confounding effect of varying crossover timepoints for clinics. The model will also include patient characteristics (Black or Hispanic/Latino, age, sex, payor) as well as random effects for clinics. Secondary patient and clinic level outcomes will be described and compared between intervention and control groups using the methods described earlier. We will also include Area Deprivation Index in the models as appropriate, calculated based on 2020 census data. Analyses will be conducted in Stata or R. All analyses will consider sex as a biological variable and race as a social construct.

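### The primary model's stated covariates omit prior failure to complete screening orders, a history the protocol itself calls higher risk; adding it is a cheap precision gain, and its absence is not an error

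*Protocol article*

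**What the plan says.** The Data analysis plan defines the patient-level primary outcome as "whether a patient identified as “due for screening” completed CRC screening" and analyses it with a generalised mixed model containing treatment, step and their interaction. On covariates it states: "The model will also include patient characteristics (Black or Hispanic/Latino, age, sex, payor) as well as random effects for clinics". It then adds: "We will also include Area Deprivation Index in the models as appropriate".

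Prior non-completion appears in three other places:

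- **Secondary outcomes.** Reach will also be counted among "those who have previously failed to complete screening referrals/orders to better understand navigation referral for those who are at higher risk of non-compliance".
- **Intervention arm core clinic components, on excess referrals.** If referrals are too many, the team will consider grading support "based on the number of previous referrals/orders that were incomplete or identification of social needs in the medical record".
- **The same section, on referral.** Providers are asked to refer patients "who have previously missed screening or require assistance to complete screening".

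All eligible patients "are not up to date on CRC screening recommendations" (Patient eligibility and initial CRC outreach).

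**The concern.** The authors single out one piece of patient history as a marker of non-completion, yet it is absent from the stated model for completion. It varies between patients within a clinic and step, so neither the clinic random effect nor the step effects can absorb it. Race/ethnicity, age, sex, payor and Area Deprivation Index are at best indirect proxies.

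In a stepped wedge with a clinic effect, much of the variance of the treatment effect comes from patient-level variation within clinic-steps. A covariate that explains part of that variation narrows the interval. It also removes chance differences between steps and conditions in the share of patients with failed orders. At stake is precision, not validity.

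**Working it through.** **Inputs from the sample-size paragraph of the Data analysis plan.** 15 clinics, 6 periods, 3 clinics crossing per step, 20 patients per clinic-step, 60% versus 70%, ICC 0.05, two-sided Wald Z at 5%.

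**Assumption.** The documents give no value for rho, the correlation between prior-order history and completion beyond the listed covariates. A range is shown.

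**Formula.** Hussey-Hughes variance for a cross-sectional stepped wedge:

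Var = I·s²·(s² + T·τ²) / [(I·U − W)·s² + (U² + I·T·U − T·W − I·V)·τ²]

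Here I = 15 and T = 6. U = 45 is the number of intervention clinic-periods. W = 495 is the sum of squared period totals, and V = 165 is the sum of squared clinic totals. So I·U − W = 180, and the second bracket is 630. Power = Φ(0.10/SE − 1.96).

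**The plan's own figure.** 45 of the 90 clinic-periods are intervention, so 20 per cell gives 900 and 900, as stated. With total variance p(1−p) and ICC 0.05, power is:

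- 73.8% at p = 0.60
- 76.0% at p = 0.65
- 79.3% at p = 0.70

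The stated 80% is therefore reproduced to within a point on the last choice. None of these uses a patient covariate.

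**Base case, p = 0.65.** Total variance is 0.65 × 0.35 = 0.2275. Then τ² = 0.05 × 0.2275 = 0.011375 and s² = 0.95 × 0.2275 / 20 = 0.010806.

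Var = 15 × 0.010806 × (0.010806 + 0.06825) / (180 × 0.010806 + 630 × 0.011375) = 0.012815 / 9.1114 = 0.001406. The SE is 3.75 points and power is 76.0%.

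**With the covariate.** Multiply s² by (1 − rho²) and leave τ² unchanged:

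| Incremental rho | SE (points) | Fall in variance | Power at 20 per cell | Gain (points) |
|---|---|---|---|---|
| 0 | 3.75 | – | 76.0% | – |
| 0.1 | 3.73 | 1% | 76.4% | 0.4 |
| 0.2 | 3.68 | 4% | 77.6% | 1.6 |
| 0.3 | 3.59 | 8% | 79.5% | 3.5 |
| 0.4 | 3.46 | 15% | 82.4% | 6.4 |

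**What these values of rho mean.** For a binary history with prevalence π and completion gap g, rho² = π(1−π)g²/0.2275. With π = 0.3, gaps of 10, 20, 30 and 40 points give rho of about 0.10, 0.19, 0.29 and 0.38. With π = 0.5 they give about 0.10, 0.21, 0.31 and 0.42.

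**Larger cells.** The sample-size paragraph calls its figure a minimum. Holding the 10-point effect, power without the covariate is 95.8% at 40 per cell and 99.4% at 60. At rho 0.3 the gain is then 1.3 and 0.3 points. The proportional fall in variance stays near 9%.

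**The case against.** The strongest reply is that nothing here is wrong. The plan prespecifies a suitable mixed model with patient covariates. Leaving out one more prognostic variable does not bias the estimate, and the article is condensed. That stands: this is an improvement to a stated list.

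Four stronger readings are tempting and are not supported.

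- **A baseline measure of the outcome has been left out.** Every eligible patient is overdue, so baseline status is constant. Prior incomplete orders are a history marker. They are undefined for patients never given an order unless those patients have their own category.
- **The variable is already in hand.** Identification is planned for reach, which concerns navigation referral in the intervention condition. The triage use is contingent. Extraction for control-period patients is not stated, though completion data come from the same EHR. The Discussion also admits difficulty in identifying stool-test orders and their results.
- **The gain is around 10 points of power.** That needs rho 0.5, or a completion gap of about 48 points even if half of patients have a failed order. The listed covariates may already explain part of any raw correlation, so only the increment counts.
- **The trial is underpowered because of the omission.** The 80% claim assumes no covariate. The 76.0% comes from where the binomial variance is evaluated.

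Two technical objections also stand. The (1 − rho²) rule belongs to a linear model; with a logit link, adjustment changes the conditional odds ratio and need not shrink its standard error. And a history frozen before baseline is 5 × 6 = 30 months old when the sixth period starts, so rho would weaken in later steps.

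**Conclusion.** The point holds as a low-cost efficiency improvement. The stated covariate list leaves out a history that the protocol itself associates with non-completion and that the clinic and step effects cannot capture. The omission does not bias the treatment effect or undermine the power statement.

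The size is uncertain. For an incremental rho of 0.1 to 0.4, the variance falls by about 1% to 15%. Power rises by about 0.4 to 6 points at the minimum cell size, and by far less with larger cells. These figures rest on an assumed rho held constant over steps, variance evaluated at p = 0.65, a common 10-point effect, and a linear approximation on the risk-difference scale.

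**What to change.** In the Data analysis plan, prespecify prior-order history as a categorical covariate of the primary model:

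- **Levels.** No prior order on record; prior order(s) with none incomplete; at least one prior order incomplete. The middle level may be thin, because the Background gives ten years between normal colonoscopies and many completers will not be due.
- **Source.** The same EHR extraction, applied identically to due patients in control and intervention periods.
- **Timing.** A look-back that ends before the six-month baseline period, so that the intervention cannot alter the covariate.
- **Reporting.** The effect as a marginal risk difference, which matches the 10-point target, with the model without this covariate as a sensitivity analysis.

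The cost is a sentence or two in the plan and a small added extraction for control-period patients. Incomplete capture of stool-test orders, patients new to the system falling in the first level, and the ageing of the history in later steps all reduce the gain. Because the covariate is fixed before any crossover, they do not bias the treatment effect. It should be fixed before outcome results are seen, since adding it afterwards would be open to challenge.

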#### Cluster-randomized controlled trial

The statistician (MM) will randomize all clinics stratified by clinic size (categorized as small, medium, large number of Black and Hispanic/Latino patients due for screening) into five, six-month steps (three clinics per step) (Fig. 2). In the stepped wedge design, after a six month baseline period where all clinics are in the control arm, clinics will cross-over to the intervention condition in sequential, staggered fashion with three clinics per step until all clinics have received the intervention. In each step, clinics randomized to intervention will receive focused implementation support for six months to tailor the patient navigation program. After the six-month step, clinic patients will continue to receive navigation and providers will continue to receive reminders and communication, but feedback will move to a quarterly cadence.

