The study was powered to detect a significant difference in the CRC screening rates between Black and Hispanic/Latino patients who receive navigation services and those who do not receive navigation. The design consists of 15 clusters and 6 steps (one baseline all clusters in control condition + 5 intervention steps) of six-month duration where 3 clusters will switch to intervention every 6-month. A sample size of an average of 120 participants (60 intervention and 60 control) per cluster and an average of 20 participants per cluster/step will achieve 80% power with 1800 participants (900 navigation and 900 control participants) to detect a conservative 10-percentage point difference in the primary outcome measure of CRC screening completion. The navigation intervention is expected to increase the screening rate from an average 60% (current data across clinics) to an average of 70%. The test statistic used was the two-sided Wald Z-test, the intra-class correlation (ICC within-clinic) was assumed to be 0.05 and the Type I error was 0.05. Sample size calculations were conducted in PASS 15 [50]. Since the navigation will be applied to all referrals and we will obtain screening completion data from EHR, this sample size will be considered as the minimum number of patients to achieve the anticipated effect size.

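### Clinics are randomised within three size strata, but the listed primary model omits the stratum: a minor loss of precision, with no bias if the strata are balanced

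*Protocol article*

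**What the plan says.** Under Cluster-randomized controlled trial, the article states that the statistician will "randomize all clinics stratified by clinic size (categorized as small, medium, large number of Black and Hispanic/Latino patients due for screening"), with three clinics allocated to each of five six-month steps.

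Under Data analysis plan, the primary outcome (screening completion, binary per patient) goes into a generalised linear mixed model with "random effects at multiple levels since observations will be nested in clinics". The fixed part is given term by term: "The model will include a treatment indicator, a fixed effect for time (steps) and their interactions", followed by "The model will also include patient characteristics (Black or Hispanic/Latino, age, sex, payor) as well as random effects for clinics". One optional covariate is added: "We will also include Area Deprivation Index in the models as appropriate". Clinic size appears nowhere in this list.

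The sample-size paragraph of the same section sets the design: "The design consists of 15 clusters and 6 steps (one baseline all clusters in control condition + 5 intervention steps"), where "3 clusters will switch to intervention every 6-month". It states that "an average of 20 participants per cluster/step will achieve 80% power with 1800 participants", for 60% against 70% completion, ICC 0.05 and a two-sided Wald Z-test at 0.05. It claims no benefit from stratification.

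**The concern.** Restricting the randomisation by a factor removes that factor's chance imbalance from the allocation. A model that ignores the factor computes its standard error as if the allocation had been unrestricted. If the factor predicts the outcome, the reported standard error is then larger than the design warrants and some power is given up.

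Size could plausibly predict completion here. The stratum counts patients due for screening, the outcome is whether such a patient completes it, and the abstract describes wide variation in baseline screening rates and patient volume across clinics. The model paragraph goes down to an optional area-level index, so the absence of the one factor that constrains the randomisation stands out.

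Efficiency is at stake, not validity. The question is how much efficiency, given that the model already has a clinic random effect.

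**Working it through.** **Inputs.** From the article: I = 15 clinics, T = 6 periods, 3 clinics crossing per step, m = 20 per clinic-step, rates 0.60 and 0.70 (difference 0.10), ICC 0.05, two-sided alpha 0.05. Assumed: five clinics per stratum with one of each size per step, equal cells, linear scale, no treatment-by-step interaction, and f, the share of between-clinic variance explained by size.

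**Formula.** The Hussey-Hughes variance with fixed periods and a random clinic intercept is

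Var = I·s²·(s² + T·τ²) / [(I·U − W)·s² + (U² + I·T·U − T·W − I·V)·τ²],

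where s² is the residual variance of a clinic-step mean and τ² the between-clinic variance. Power = Φ(0.10/√Var − 1.96).

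- U (treated cells) = 3·(5+4+3+2+1) = 45
- W (sum of squared period totals) = 0² + 3² + 6² + 9² + 12² + 15² = 495
- V (sum of squared clinic totals) = 3·(25+16+9+4+1) = 165
- I·U − W = 675 − 495 = 180
- U² + I·T·U − T·W − I·V = 2025 + 4050 − 2970 − 2475 = 630

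Treated patients: 45·20 = 900 of 1800, as the plan states.

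**Plan's own figure.** With total variance 0.70·0.30 = 0.21, s² = 0.21·0.95/20 = 0.009975 and τ² = 0.21·0.05 = 0.0105. Then Var = 0.010919/8.4105, SE = 0.0360 and power = 79.3%, close to the stated 80%. With the pooled variance 0.65·0.35 = 0.2275, s² = 0.010806 and τ² = 0.011375. Then Var = 0.012815/9.1114, SE = 0.0375 and power = 76.0%.

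**Effect of adding the stratum.** Replace τ² by τ²·(1 − f). With balanced strata the stratum terms are orthogonal to treatment, and exact GLS with two stratum indicators gives the same adjusted SEs.

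| f (assumed) | SE, pooled variance | SE ratio | Power, pooled | Power, variance 0.21 |
|---|---|---|---|---|
| 0 | 0.0375 | 1 | 76.0% | 79.3% |
| 0.10 | 0.0373 | 0.996 | 76.4% | 79.6% |
| 0.20 | 0.0372 | 0.991 | 76.8% | 80.0% |
| 0.25 | 0.0371 | 0.988 | 77.0% | 80.2% |
| 0.40 | 0.0366 | 0.977 | 77.9% | 81.0% |
| 0.50 | 0.0363 | 0.968 | 78.7% | 81.8% |
| 0.75 | 0.0348 | 0.927 | 82.0% | 84.9% |

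**What omission does to validity.** In the same GLS set-up, the estimate without the stratum has zero bias. Its reported SE is 0.0375, against a true SE of 0.0371, 0.0368 and 0.0364 at f = 0.25, 0.50 and 0.75, so it is mildly conservative.

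**What the clinic intercept already does.** An analysis with no clinic effect would have a true SE of 0.0572, against 0.0375 with the planned one.

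**Larger cells.** The article treats 20 per clinic-step as a minimum. Doubling m to 40 (illustrative) halves s² to 0.005403. At f = 0.50 the SE goes from 0.0271 to 0.0265, a fall of 2.1% instead of 3.2%. Power goes from 95.8% to 96.5%, a gain of 0.7 points instead of 2.7.

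**Simulation** (2000 runs per setting, REML on clinic-step proportions), without against with the stratum:

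| f | Power | Type I error |
|---|---|---|
| 0.25 | 77.3% vs 77.9% | 5.8% vs 6.2% |
| 0.50 | 76.5% vs 79.4% | 4.1% vs 5.2% |
| 0.75 | 77.4% vs 82.8% | 4.4% vs 6.3% |

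The Monte Carlo standard error at 5% is √(0.05·0.95/2000) ≈ 0.5 points.

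**The case against.** The strongest reply is that this is one paragraph of a condensed article. It does not say its list of terms is complete, and a stratification covariate is often left to an analysis plan, which is not shown here. It is also fair that the gain rests on an assumed share f, and that over f = 0.10 to 0.50 it is smaller than the spread from the choice of binomial variance alone (73.8% with 0.60·0.40 to 79.3% with 0.70·0.30). These points hold the matter at minor severity. They do not remove it, because the article does set out its model term by term and the design factor is not among them.

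Three stronger readings are tempting, and the documents do not support them.

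- *Size-related variance is left in the residual error.* It is not. The listed model has random clinic effects and every clinic contributes both control and intervention periods. The variance sits in the clinic component and reaches the treatment SE only through the limited between-clinic information.
- *The primary test is biased or anti-conservative.* With balanced strata the bias is zero and the reported SE is slightly too large, not too small.
- *Adjustment is free.* Two cluster-level parameters are spent on 15 clinics, and the simulated type I error was higher with the stratum in all three settings, so part of the simulated power gain may reflect that.

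The article gives no stratum counts, so exact balance (five clinics per stratum) is itself an assumption.

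**Conclusion.** The mismatch between the randomisation and the listed model stands, as a minor point of efficiency. Under the plan's inputs with pooled variance, including the stratum raises power by about 0.4 to 2.7 points if size explains 10–50% of the between-clinic variance. If size explains nothing, nothing is lost. A gain of 5 to 6 points needs a share of about 75%, for which the article gives no support. With more than 20 patients per clinic-step the gain is smaller still.

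The figures rest on the assumed f, one clinic of each size per step, equal cells, a linear scale and no treatment-by-step interaction. They show the order of magnitude and are not exact for the planned binary mixed model. The stated 80% power does not depend on this adjustment.

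**What to change.** Add the three-level clinic-size stratum used for randomisation as a fixed effect in the primary model, and name it alongside the other terms before outcome data are analysed. Its inclusion is then not a later, data-dependent choice.

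The cost is one line of text and no new data, since size is known for every clinic before randomisation. The small downside is two cluster-level parameters with only 15 clinics, so pair the change with a small-sample correction for the treatment test. If an existing analysis plan already includes the stratum, nothing more is needed.

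### Two-sample tests between conditions ignore clinic and calendar time, the sentence on secondary outcomes leaves room for them, and reach and adoption have no control-phase value to be compared with

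*Protocol article*

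**What the plan says.** All of this is in the protocol article.

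- **Data analysis plan, two-sample tests.** After the sentences on summarising patient characteristics: "Initial comparisons between the intervention and control groups will be done using two-sample test statistics such as t-test and Chi-square as appropriate".
- **Data analysis plan, mixed model.** For the primary outcome: "The model will include a treatment indicator, a fixed effect for time (steps) and their interactions", with patient characteristics "as well as random effects for clinics".
- **Data analysis plan, secondary outcomes.** Directly after the model: "Secondary patient and clinic level outcomes will be described and compared between intervention and control groups using the methods described earlier". The sentence does not say which earlier method is meant and makes no exception for any outcome.
- **Secondary outcomes, reach.** "Reach will be assessed as the percentage of eligible Black and Hispanic patients at each clinic who received a referral for navigation". A second measure covers engagement among the patients so referred.
- **Secondary outcomes, adoption.** "Adoption will be assessed by the percentage of providers who referred eligible patients for navigation".
- **Patient eligibility and initial CRC outreach.** "For clinics in the intervention phase, the provider will have the option to refer patients to navigation". The section on core clinic components likewise describes the request to refer as part of what follows assignment to the intervention arm.

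**The concern.** A two-sample test assumes independent patients and groups that are exchangeable in time. Neither holds here. Patients are nested in 15 clinics, each clinic appears on both sides of the comparison, and control time comes first by design. The Discussion itself expects secular change in screening. P-values from such tests would have the wrong error rate, and part of any time trend would be credited to the intervention.

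The second issue is separate. A navigation referral cannot be made until a clinic has crossed over. Comparing the referral percentage with control steps therefore shows only that the referral route was opened. Significance would be automatic and would say nothing about how well the programme was implemented.

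**Working it through.** **Inputs.** From the Data analysis plan: "The design consists of 15 clusters and 6 steps (one baseline all clusters in control condition + 5 intervention steps"), three clinics crossing per step, 20 patients per clinic-step, rates of 60% and 70%, ICC 0.05, two-sided alpha 0.05. Assumptions added here: equal cell sizes, different patients in each step, one clinic-level ICC, mean rate 65%.

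**1. Layout and the plan's own figures.** Control clinic-steps: 15 + 12 + 9 + 6 + 3 = 45. Intervention clinic-steps: 3 + 6 + 9 + 12 + 15 = 45. Times 20, this gives 900 + 900, as the plan states. The Hussey-Hughes variance for this layout gives a standard error of 0.0375 and power of 76.0% with the variance taken at 65%, and 79.3% with the variance at 70%, against the stated 80%. The power figure is not in dispute; the check only confirms how the design inputs are to be read.

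**2. Calendar-time imbalance.**
- Intervention: (3×2 + 6×3 + 9×4 + 12×5 + 15×6)/45 = 210/45 = 4.67.
- Control: (15×1 + 12×2 + 9×3 + 6×4 + 3×5)/45 = 105/45 = 2.33.
- Gap: 2.33 steps × 6 months = 14 months.

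**3. Variance of the raw difference in proportions.** By crossover group, a clinic has 5, 4, 3, 2 or 1 intervention steps and 1, 2, 3, 4 or 5 control steps. Its net weight in the difference is therefore (4, 2, 0, −2, −4)/45, with three clinics in each group.
- Clinic part: 3 × (16 + 4 + 0 + 4 + 16)/45² = 120/2025. With a total variance of 0.65 × 0.35 = 0.2275, the between-clinic variance is 0.05 × 0.2275 = 0.011375. Contribution: 0.000674.
- Patient part: 90 cells, each with weight 1/45 and variance 0.95 × 0.2275/20 = 0.010806. Contribution: 0.010806 × 90/2025 = 0.000480.
- True variance: 0.001154.
- Variance the test assumes: 0.2275 × 2/900 = 0.000506.
- Ratio: 2.28. The rate cancels from it, so the ratio depends only on the ICC and the cell size.

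**4. Type I error with no effect and no trend.** 2 × [1 − Φ(1.96/√2.28)] = 2 × [1 − Φ(1.297)] ≈ 19.5%. A simulation of the same layout (5,000 runs, 60% rate) gave 19.7%; with ICC 0 it gave 5.1%, as it should. For other assumed ICCs the simulation gave 7.4% (ICC 0.01) and 29.1% (ICC 0.10).

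**5. Effect of a trend (assumed values only).** The bias is 2.33 times the change per step. Type I error is simulated at ICC 0.05.

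| Assumed rise per step | Bias in the difference | Type I error |
|---|---|---|
| 0.5 points | about 1.2 points | 22.6% |
| 1 point | about 2.3 points | 28.5% |
| 2 points | about 4.7 points | 53.3% |

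**6. Reach and adoption.** The numerator of each is a referral to study navigation, and the referral option belongs to the intervention phase. The control value is thus 0 in all 45 control clinic-steps. A chi-square test would only register that fact. A logistic mixed model would meet complete separation and yield no finite treatment effect. Neither earlier method gives a usable contrast.

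**The case against.** The strongest reply is that the protocol nowhere commits secondary outcomes to t-tests or chi-square. The mixed model is the nearer antecedent of the sentence on secondary outcomes, and the next sentence speaks of models in the plural. The sentence on two-sample tests follows the description of patient characteristics and may be no more than a balance check. This stands: a reader might infer that the secondary analyses are fixed as unadjusted tests, and the text does not support that. It allows both readings. What remains is that two-sample tests between conditions are affirmatively planned at least once, that even as balance checks they ignore clinic and step, and that the later sentence does not exclude them.

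Second, under Conceptual frameworks only effectiveness is defined by a contrast of conditions, and that section and Secondary outcomes already plan reach by clinic, prior non-completion, insurance, age, race/ethnicity and language. This also stands. It would be wrong to infer that the plan yields no information on implementation. The defect is confined to a general comparison sentence with no exception for these outcomes.

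Third, the type I figures use the primary outcome's ICC and rate, although that outcome is analysed by the mixed model. That is correct, and they are an illustration; the document gives no ICC for any secondary outcome. Nor does it supply a trend. A reader might take one from the 58.7% and 68.3% in the Background, but the latter is a goal for 2030, not an observed or forecast rate.

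**Conclusion.** The point holds in a limited form. The planned two-sample tests do not suit this design, and the sentence on secondary outcomes leaves room for them. With the primary outcome's parameters, 20 patients per clinic-step and no trend, the variance is understated by a factor of about 2.3 and type I error is about 19 to 20%. The size for any particular secondary outcome is unknown, because it depends on that outcome's ICC, the cell sizes actually reached and the trend.

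The comparison of reach and adoption with control is uninformative whichever earlier method is meant. One caveat applies: Formative work and Patient navigation strategy mention an existing navigation programme at one hospital-based clinic, and the article does not say whether that clinic is among the 15. If it is, some navigation could occur there in control steps, but this would not make the contrast meaningful.

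No inference about the primary analysis follows, since it is assigned to a model with step and clinic terms.

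**What to change.** Three changes to the Data analysis plan:

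1. Keep the summaries by condition descriptive and drop the two-sample p-values. Standardised differences by step would serve, in steps 2 to 5, where both conditions are present.
2. For secondary outcomes measurable in both conditions, replace the reference to earlier methods with the mixed model by name, with step fixed effects and clinic random effects.
3. Exempt reach and adoption from the comparison between conditions. Report them within intervention clinic-steps only, with confidence intervals and by time since crossover (the six months of focused support against the later phase), alongside the breakdowns already planned.

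The cost is wording in the analysis plan. Conduct, data collection and sample size do not change.
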